### Safety Observations

During the trial, each participant will receive safety monitoring. All adverse events will be forwarded to the ethics committee. They will review all documented harms during the trial and adjudicate them with regard to causality. The observations are listed below:

Vital signs: Body temperature, heart rate, blood pressure, and respiration (once at each follow-up visit)Blood routine, urine routine, stool routine plus occult blood (once before and after treatment, respectively; twice in total)Hepatic function (alanine aminotransferase, aspartate aminotransferase, total bilirubin, alkaline phosphatase, gamma-glutamyl transferase), renal function (serum creatinine, blood urea nitrogen) (once before and after treatment, respectively; twice in total)Electrocardiogram (once before and after treatment, respectively; twice in total)Severity and incidence of adverse events (recorded in detail at any time)

The schedule for the enrollment, interventions, and assessment is summarized in Table 3.

**Table 4 table3:** Schedule of enrollment, interventions, and assessments in the trial.

Time point		Study period (week)				
		Enrollment		Allocation	Post-allocation	Follow-up
		Washout (–3 to –1)	Run-in (–1)	0	12	12

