Aerobic exercise intensity will be determined using the Borg Category-Ratio 0-10 Scale (Borg CR10 Scale) modified for dyspnea, as recommended by the American College of Sports Medicine guidelines for patients with pulmonary diseases [23]. The exercise intensity will start from Rating 3 (equivalent to 53% peak work rate, ie, moderate intensity) in the first 2-4 weeks and progressively increase to Rating 6 (equivalent to 80% peak work rate, ie, vigorous intensity). Exercise intensity and session duration will be adjusted according to each patient’s response and tolerance. Lighter intensities than Rating 3 may be adopted when there is a need (eg, for those with severe conditions). Patients will be given specific and standardized instructions on the ratings in advance. A pulse oximeter (Beurer PO 40, Beurer GmbH) will be used to monitor oxygen saturation in the initial exercise sessions to avoid exercise-induced oxyhemoglobin desaturation. In terms of intensity of resistance training, a practical approach to determine the appropriate intensity will be adopted, in which workloads will be set at levels that evoke local muscular exhaustion in 6 to 12 repetitions, as the one repetition maximum approach may overestimate or underestimate the optimal resistance for individuals [20,31]. Progressive target goals and detailed training plans will be set up together with each patient based on their physiological measurement results [21].

The exercise intervention will be delivered and supervised by experienced instructors. We will recruit persons who have been educated in either exercise science or rehabilitation. Each exercise session will be facilitated by two instructors dedicated to a group of 5-7 patients through the web-based platform in our International Rehabilitation Network Center for Patients With COVID-19. They will also be responsible for monitoring developments and training during the intervention.

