#### Waiting List Control

The waiting list control sign will be adopted to conceal the allocation results from the patients as well as to reduce selection and confounding bias and increase the participants’ adherence to the study. Patients in the waiting list control group will receive no treatment in the study period (including a 12-week intervention period and a 12-week follow-up period). However, they will receive Chinese herbal medicines after the completion of the study (ie, after the third wave of measurements in the 25th week).

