### Data Management and Storage

The original medical records will be kept intact by the site investigators as the original documents of the clinical trial. All researchers will receive training regarding data management. Web-based application and user sessions will be encrypted between the server and client browser through the use of industry standard secure sockets layer (SSL) certificates. The data will be entered into the electronic case report form and the database will be established before recruitment. The investigators will be responsible for verifying the accuracy of the data. Data locking will be completed by the data management team, and the researchers will not be able to modify the data. All research documents, including paper and electronic documents, will be retained for at least 5 years after publication. All individual participant data collected during the trial will be deidentified and made available to anyone who wishes to access the data immediately following publication.

A Data and Safety Monitoring Board (DSMB) has been set up to review the protocol and the research data. The DSMB will meet regularly to review the protocol according to ethical and safety standards, monitor the safety of the trial, and monitor the authenticity and completeness of the data based on the study design. The DSMB will review the progress of the trial, determine adverse events, and have the authority to decide whether the study needs to end early.

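### Adverse events are recorded at any time with no common enquiry stated, so exercise versus non-exercise comparisons of their incidence are open to ascertainment bias against exercise

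*Protocol article*

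**What the plan says.** All statements are in the protocol article.

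- **Scope.** Safety Observations covers every arm: "During the trial, each participant will receive safety monitoring".
- **Adverse events.** The same list includes "Severity and incidence of adverse events (recorded in detail at any time"). No interval, script or person responsible for asking is given.
- **Visit-based item.** "Vital signs: Body temperature, heart rate, blood pressure, and respiration (once at each follow-up visit").
- **Treatment-based items.** The blood, urine and stool routine, the hepatic and renal tests and the ECG are each set "once before and after treatment, respectively; twice in total".
- **Contact in the exercise arms.** There are 36 supervised sessions over 12 weeks and 12 education sessions (Textbox 1, Table 1). "Each exercise session will be facilitated by two instructors dedicated to a group of 5-7 patients", and these instructors also monitor developments during the intervention. The programme adds remote vital-sign monitoring, pulse oximetry in the initial sessions, counselling and a call center (Structure of the Exercise Intervention).
- **Contact in the other arms.** The granules are taken by patients themselves (Chinese Herbal Medicines). "Patients in the waiting list control group will receive no treatment in the study period" (Waiting List Control). The only scheduled contacts described after baseline are the assessments at weeks 13 and 25 that all arms share (Outcomes).

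**The concern.** The number of adverse events on record depends on how often they occur and on how often someone is in a position to hear of or see them. A rule that accepts events whenever they arise, without a fixed enquiry, leaves the second factor to the contact schedule of each arm. Here that schedule is part of the randomized treatment. An exercise patient is seen by an instructor three times a week, with some physiological signs measured live. A herbs-only or waiting-list patient may be asked nothing until week 13 and must then recall 12 weeks.

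The blinding of outcome assessors (Blinding) does not help with events noticed in a session, because the instructors know who is exercising.

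At stake is the harm side of the combination-versus-single-treatment question. A home exercise programme could appear to cause minor events that were merely observed more closely, and the combination could look less safe than herbs alone for the same reason.

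**Working it through.** The plan states no figure for adverse-event capture, so there is none to reproduce. The check counts described contacts and then illustrates what a gap in capture would do.

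**1. Scheduled contacts after baseline**

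- Exercise arms: 36 sessions + 2 assessments = 38. If the 12 education sessions are counted separately, 36 + 12 + 2 = 50. They are held with the first session of each week, so 38 is the stricter count. Counselling and call-center contacts are not counted.
- Herbs-only and waiting-list arms: 2.
- Ratio: 38/2 = 19 to 50/2 = 25.
- Before the week-13 visit the described counts are 36 to 48 against 0. From week 13 on, the scheduled assessments are the same in all arms, so the gap belongs to the intervention period.

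**2. Which contrasts are exposed**

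| Contrast | Described contacts | Balanced? |
|---|---|---|
| Combination vs herbs-only | 38–50 vs 2 | No |
| Exercise-only vs waiting list | 38–50 vs 2 | No |
| Combination vs waiting list | 38–50 vs 2 | No |
| Exercise-only vs herbs-only | 38–50 vs 2 | No |
| Combination vs exercise-only | 38–50 vs 38–50 | Yes |
| Herbs-only vs waiting list | 2 vs 2 | Yes |

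The last two rows are the contrasts that isolate the herbs.

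**3. Illustrative size, with no true difference between arms.** All capture rates are assumptions; none is in the document.

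*(a) One event or none per patient.* Recorded risk = true risk × capture, so the apparent risk ratio is the ratio of captures:

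- 95% vs 90%: 0.95/0.90 = 1.06
- 95% vs 70%: 0.95/0.70 = 1.36
- 95% vs 50%: 0.95/0.50 = 1.90

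*(b) Recurrent events.* With a true rate of 1 event per patient over 12 weeks, P(at least one recorded) = 1 − exp(−rate × capture):

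- capture 90%: 1 − exp(−0.9) = 0.593
- capture 50%: 1 − exp(−0.5) = 0.393; ratio 0.593/0.393 = 1.51
- capture 30%: 1 − exp(−0.3) = 0.259; ratio 0.593/0.259 = 2.29

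**4. Chance of a spurious finding under (a).** With n = 43 per arm (Sample Size Calculation) and two-sided α = 0.05, the chance of a significant excess in the exercise arm is about Φ((d − 1.96·SE₀)/SE₁). Here d is the difference in recorded risks, SE₀ the pooled and SE₁ the unpooled standard error. Example: true risk 20%, capture 95% vs 50%, recorded risks 0.19 and 0.10. Then d = 0.09, SE₀ = 0.0759, SE₁ = 0.0753, and Φ(−0.78) = 0.22.

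| True risk | 95% vs 90% | 95% vs 70% | 95% vs 50% |
|---|---|---|---|
| 20% | 3% | 9% | 22% |
| 40% | 4% | 16% | 45% |

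The nominal value in one direction is 2.5%. A small capture gap does almost no harm; a large one does.

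**5. Timing of the laboratory and ECG tests.** Two tests around treatment have no literal anchor in an arm untreated until after the week-25 measurements. However, the article uses treatment words as time labels elsewhere. Blood Biochemistry draws blood at pretreatment and posttreatment without excepting any arm, and the schedule table ticks safety in every column without distinction by arm. Baseline and the end of the 12-week period is the evident meaning.

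**The case against.** The strongest reply is that this is a condensed article. Recording at any time may only mean throughout the trial, and who asks, how and when are matters that a full protocol usually settles. Contact that is not described is not contact that does not exist. The article also announces no between-arm test of harms: they are in none of the listed objectives, and Statistical Analysis does not mention them. Part of this stands. If the full protocol has a common enquiry, the sponsor need only state it, and no planned test is shown to be wrong. But the article does fix a capture rule, names incidence as an observation, and describes very unequal contact. Any by-arm table of events built on that rule inherits the imbalance, whether or not a p-value is attached.

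Three stronger readings are tempting and are not supported:

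- *Harms cannot be compared between arms at all.* Every participant is monitored, vital signs are tied to visits, and both contrasts that isolate the herbs have matched described contact.
- *The herbal arms lack a concurrent laboratory control.* Even if the waiting-list tests were taken literally to fall outside the study, the exercise-only arm takes no herbs and is tested around the same 12 weeks. Combination versus exercise-only remains a randomized, concurrent comparison.
- *The article contradicts itself on who judges adverse events.* The ethics committee adjudicates causality (Safety Observations), while the DSMB is to "determine adverse events, and have the authority to decide whether the study needs to end early" (Data Management and Storage). The latter does not mention causality, so the tasks may differ and no clear contradiction is shown.

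**Conclusion.** The point holds in a limited form. Adverse-event incidence, captured as the article states, is open to ascertainment bias against exercise in the comparisons of an exercise arm with a non-exercise arm. That bias would arise mainly in the 12-week intervention period. The contact gap, 19- to 25-fold as described, makes the direction likely. The size depends wholly on the assumed capture gap: the false risk ratio is about 1.06 if capture is nearly equal and up to about 2.3 if one visit recovers only 30% of events. The conclusion also assumes that no common enquiry exists outside the article. The efficacy analysis and the sample size of 172 are untouched. The timing of the laboratory and ECG tests is a matter of wording, not a lost control group.

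**What to change.** In Safety Observations:

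1. State that the same standard adverse-event question is put to all four arms at the same fixed weeks. A smartphone prompt would serve, since being a smartphone user is an inclusion criterion (Eligibility Criteria).
2. Use the events solicited in this way for between-arm comparisons of incidence. Report events first detected in exercise sessions separately. Report all serious events for every arm however they came to light, so that restricting the comparison does not drop any.
3. Replace the treatment-based timing of the blood, urine and stool routine, the hepatic and renal tests and the ECG with baseline and week 13 in all four arms.

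If the full protocol already contains a common enquiry, a sentence pointing to it replaces items 1 and 2, provided that it also says which events enter the comparison.

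The cost is some protocol wording, a short periodic question for patients, and more minor events to process. The number of laboratory and ECG test sets per patient stays at two, and no sample size or treatment changes.

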**Enrollment**						
	Eligibility screen	✓				
	Informed consent	✓				
	Randomization			✓		
	Allocation			✓		
**Intervention**						
	Cardiorespiratory exercise plus Chinese herbal medicines				✓	
	Cardiorespiratory exercise				✓	
	Chinese herbal medicines				✓	
	Waiting list					
**Assessment**						
	Cardiorespiratory fitness				✓	✓
	Dyspnea				✓	✓
	Body composition				✓	✓
	Lung function test				✓	✓
	Cardiopulmonary exercise test				✓	✓
	Blood biochemistry tests				✓	✓
	Gut microbiome				✓	✓
	Glucose, fructose, and related metabolites				✓	✓
	Metabolomics-related measurement of depression				✓	✓
	Quality of life and other mental health-related measures				✓	✓
	Safety	✓	✓	✓	✓	✓

### Infectious Control

Prior to and following the testing procedures, all equipment will be subjected to rigorous disinfection methods for clinical populations as outlined by the Guidelines on Infection Control Practice in the Clinical Setting of the Department of Health [49]. Further to this, individuals involved in testing and data collection will be required to wear the necessary protective clothing and observe personal hygiene regulations as further outlined in the document [49].

### Data Management and Storage

The original medical records will be kept intact by the site investigators as the original documents of the clinical trial. All researchers will receive training regarding data management. Web-based application and user sessions will be encrypted between the server and client browser through the use of industry standard secure sockets layer (SSL) certificates. The data will be entered into the electronic case report form and the database will be established before recruitment. The investigators will be responsible for verifying the accuracy of the data. Data locking will be completed by the data management team, and the researchers will not be able to modify the data. All research documents, including paper and electronic documents, will be retained for at least 5 years after publication. All individual participant data collected during the trial will be deidentified and made available to anyone who wishes to access the data immediately following publication.

A Data and Safety Monitoring Board (DSMB) has been set up to review the protocol and the research data. The DSMB will meet regularly to review the protocol according to ethical and safety standards, monitor the safety of the trial, and monitor the authenticity and completeness of the data based on the study design. The DSMB will review the progress of the trial, determine adverse events, and have the authority to decide whether the study needs to end early.

### Data Protection

All data protection and patient anonymity considerations will apply throughout the experimental and postexperimental period. All patients prior to participation will be required to complete an informed consent form, clearly outlining experimental procedures and information relating to the study. All data will be anonymized with the unique experimental IDs provided to the patients. Data collected will be stored in a secure location under lock and key. Computer-generated information will be given specific passwords, with access granted to the principal investigator. Patients will be informed that they can withdraw from the study at any time. Prior to data collection, ethical approval will be obtained from the ethics committee. All data collection procedures, confidentiality issues, and patient integrity will be subject to methodological rigor as outlined by the data protection act.

### Sample Size Calculation

Aiming to achieve a large effect size of 0.8, based on a meta-analysis of effectiveness of exercise interventions on dyspnea and exercise capacity in patients with pulmonary fibrosis diseases [28], using a significance level of 0.05, power level of 90%, and 20% drop-out rate, a sample size of 172 patients (43 per group) was preliminarily estimated for the study. The meta-analysis result was chosen because there is no similar rehabilitation program available that combines exercise and Chinese herbal medicine. Furthermore, the outcome variables in that meta-analysis are similar to our primary outcomes. Given that the effects of Chinese herbal medicine were not considered, the final sample size will be re-estimated using preliminary outcomes from the pilot study.

### Statistical Analysis

A generalized linear mixed model will be used to compare between-group differences in changes of outcome variables at the 12- and 24-week periods of the study, where group and time are the two factors of interest. Mediating effects of the gut microbiome and immune function tests will be determined by fitting linear regression models for pulmonary and other outcomes, respectively. A significance level of 0.05 will be adopted (two-tailed test). Intention-to-treat procedures will be applied to the data sets obtained. Missing data will be imputed using multiple imputations with chained equations, except for those from dropouts, which will be imputed with the baseline data. Data will be scrutinized for normal distribution prior to data analysis. Sensitive analyses, such as per-protocol analysis, as-treated analysis, and analysis for complete cases, will only be performed to assess the robustness of the data analyses.

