**Methods:**

In this triple-blinded, randomized, parallel-group, controlled clinical trial, we will recruit adult patients with COVID-19 who have been discharged from hospital in Hong Kong and are experiencing impaired lung function and pulmonary function. A total of 172 eligible patients will be randomized into four equal groups: (1) cardiorespiratory exercise plus Chinese herbal medicines group, (2) cardiorespiratory exercise only group, (3) Chinese herbal medicines only group, and (4) waiting list group (in which participants will receive Chinese herbal medicines after 24 weeks). These treatments will be administered for 12 weeks, with a 12-week follow-up period. Primary outcomes include dyspnea, fatigue, lung function, pulmonary function, blood oxygen levels, immune function, blood coagulation, and related blood biochemistry. Measurements will be recorded prior to initiating the above treatments and repeated at the 13th and 25th weeks of the study. The primary analysis is aimed at comparing the outcomes between groups throughout the study period with an α level of .05 (two-tailed).

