Evaluate the effects of cardiorespiratory exercise and Chinese herbal medicine, both individually and in a combination, on rehabilitation on pulmonary function among patients with COVID-19 through four intervention groups, including a cardiorespiratory exercise plus Chinese herbal medicines group, a cardiorespiratory exercise group in isolation, a Chinese herbal medicines group, and a waiting list control group (primary outcome). We hypothesize that the combination of cardiorespiratory exercise and Chinese herbal medicines will more greatly facilitate the rehabilitation of patients with COVID-19.Reveal whether and how the gut microbiome plays a role in the effects of cardiorespiratory exercise and Chinese herbal medicines, both individually and in combination, on the rehabilitation of impaired pulmonary function. We hypothesize that the combination of cardiorespiratory exercise and Chinese herbal medicines will better modulate the gut microbiome and the related metabolites and thus better mediate the effects.Assess the effects of cardiorespiratory exercise and Chinese herbal medicines on immune functions, both individually and in combination, on the rehabilitation of other relevant symptoms and signs of COVID-19. We hypothesize that the combination of cardiorespiratory exercise and Chinese herbal medicines will better modulate the immune function and thus better mediate the effects.Evaluate the effects of cardiorespiratory exercise and Chinese herbal medicines, both individually and in combination, on recovery from mental health-related outcomes (loneliness, stress, anxiety, depression) and on quality of life (QoL). We hypothesize that the combination of cardiorespiratory exercise and Chinese herbal medicines will better help postdischarge patients in recovery from mental health-related outcomes and improve their QoL.Assess the lasting effects of cardiorespiratory exercise and Chinese herbal medicines after a 12-week follow-up period. We hypothesize that some effects (eg, dyspnea, mental health-related outcomes, QoL) will be sustainable, while others (outcomes sensitively responded to cardiorespiratory exercise, eg, physical fitness, lung function) will partially relapse after the intervention cessation.

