### Outcomes

Table 2 lists a description of the outcomes and other measures, which are not exhaustive. All measurements will be recorded at baseline and repeated at the 13th and 25th weeks of the study. Patients will be assessed for risk prior to data collection. Further information from patients using appropriate data collection methodologies, including clinical symptoms, treatment history, comorbidities, physical activity, nutrition, and other potential variables, will be obtained and adjusted for during data analysis.

**Table 2 table2:** Description of the outcome measures.

Measure		Outcomes
Cardiorespiratory fitness		Six-minute walk test Performance time test
Dyspnea		Borg Category-Ratio 0-10 Scale (Borg Dyspnea Scale)
Body composition		BMI Waist circumference Stature Body mass Segmental muscle mass Anatomical circumference
Lung function test		Forced vital capacity Forced expiratory volume 1 Forced expiratory volume 1/forced vital capacity Fractional exhaled nitric oxide DLCO^a^
Cardiopulmonary exercise test/blood gas		VE^b^ VCO_2_^c^ VO_2_^d^/PCO_2_^e^ PO_2_^f^

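### The analysis compares changes from baseline and does not name the baseline value as a covariate, which costs precision but does not cause bias

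*Protocol article*

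**What the plan says.** The Statistical Analysis section of the protocol article plans: "A generalized linear mixed model will be used to compare between-group differences in changes of outcome variables at the 12- and 24-week periods". It adds: "where group and time are the two factors of interest". The test level is 5%: "A significance level of 0.05 will be adopted (two-tailed test").

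Under Outcomes: "All measurements will be recorded at baseline and repeated at the 13th and 25th weeks of the study". The same section says that clinical symptoms, treatment history, comorbidities, physical activity, nutrition and other possible variables will be adjusted for. The baseline value of the outcome being analysed is neither named nor excluded.

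The first objective in the Introduction is to evaluate exercise and herbal medicine "both individually and in a combination, on rehabilitation on pulmonary function among patients with COVID-19 through four intervention groups". Its hypothesis is that the combination does better; no comparator is named. The arms are both treatments, exercise only, herbal medicine only, and an untreated waiting list. The Abstract calls the design parallel-group.

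**The concern.** When change from baseline is the response and baseline is not a covariate, the analysis in effect fixes the slope of follow-up on baseline at 1. With equal variances at the two times, the best slope is r, which is below 1. Subtracting the whole baseline value therefore over-corrects for chance imbalance and adds baseline noise to the comparison. A longitudinal model with group, time and their interaction, and a free baseline mean for each arm, has the same property.

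At stake is precision in a trial with 34 evaluable patients per arm expected after dropout. The baseline values that would recover it are already being collected.

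**Working it through.** **1. The plan's own sample size.** Inputs from Sample Size Calculation: "Aiming to achieve a large effect size of 0.8, based on a meta-analysis of effectiveness of exercise interventions", and "using a significance level of 0.05, power level of 90%, and 20% drop-out rate". The Abstract gives the test as two-sided.

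- Two-sample t test, d = 0.8, two-sided 0.05, power 90%: 33.83, rounded up to 34 per arm.
- Dropout: 34 / (1 − 0.20) = 42.5, rounded up to 43 per arm.
- Four arms: 4 × 43 = 172.

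This reproduces the stated 43 per group and 172 exactly. The trial is therefore sized on one unadjusted comparison of two arms, with SE √(2/34) = 0.243 SD.

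**2. Change score against baseline adjustment.** Take a continuous outcome with the same SD σ at baseline and follow-up, and correlation r.

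- Variance of a change score: 2σ²(1 − r).
- Residual variance after conditioning on baseline: σ²(1 − r²).
- Ratio: (1 − r)(1 + r) / [2(1 − r)] = (1 + r)/2, which is below 1 for every r < 1.

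The document gives no r, so a range is shown. Power is for one pairwise comparison, 34 v 34. The document does not say which SD the 0.8 refers to; the last two columns take it as the SD of change scores.

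| Assumed r | Variance ratio | SE ratio | Power, change score | Power, baseline-adjusted |
|---|---|---|---|---|
| 0.3 | 0.65 | 0.81 | 90% | 98% |
| 0.5 | 0.75 | 0.87 | 90% | 96% |
| 0.7 | 0.85 | 0.92 | 90% | 94% |
| 0.9 | 0.95 | 0.97 | 90% | 91.5% |

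If 0.8 is in raw-score SDs instead, power at r = 0.3 is 78% with change scores and 93% with adjustment. At r = 0.5 the figures are 90% and 96%. At r = 0.7 and above both exceed 98%.

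**3. Does the four-level group factor lose anything?** One simulated data set of 172 patients (43 per arm) was fitted twice, with a four-level group and with exercise × herbal medicine.

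- Residual sum of squares 128.71 on 168 df in both.
- Interaction 0.181 (SE 0.267) in both.
- Exercise alone v waiting list 0.393 (SE 0.189) in both.
- The marginal exercise effect, taken as a contrast of the four-level fit, is 0.483 (SE 0.1335). The additive two-factor model gives 0.483 (SE 0.1333).

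These are the same model in two codings. All arm contrasts, the interaction and the marginal effects are available from either.

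**4. What each contrast can detect with 34 evaluable per arm.** Detectable difference = (1.960 + 1.282) × SE.

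| Contrast | SE (SD units) | Detectable at 90% | Power at 0.8 SD | Power at 0.4 SD |
|---|---|---|---|---|
| Two arms | √(2/34) = 0.243 | 0.79 | 91% | 37% |
| Marginal main effect | √(1/34) = 0.171 | 0.56 | 99.6% | 64% |
| Interaction | √(4/34) = 0.343 | 1.11 | 64% | 21% |

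The gain from 0.79 to 0.56 SD comes from changing the question to an average over the other treatment. It does not come from recoding the group factor.

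**The case against.** **The wording does not strictly exclude baseline adjustment.** A mixed model with a common baseline mean can also be described as comparing changes between groups, and it is about as efficient as covariate adjustment. The adjustment list under Outcomes is open-ended. This stands, and it limits the point: the loss applies to the plan read as written, and an analyst could avoid it without contradicting the text.

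**The gain may be small.** It is 5% of the variance at r = 0.9. The only related figure in the document is the six-minute walk test reliability of 0.88–0.91. That is test-retest reliability, not a 12-week correlation, and it concerns one outcome. This stands as a limit on size, not on direction.

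**Three stronger readings that a reader might infer are not supported.**

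- *That one four-level factor wastes half the information in a 2×2 layout, or cannot test single and combined effects.* The codings are equivalent (step 3). Comparing arms is a direct reading of the first objective and agrees with a parallel-group trial sized on one pairwise comparison. Making marginal main effects primary is a debatable trade-off: they equal the individual effects only without interaction, and the interaction test is too weak to check that.
- *That leaving the contrasts unnamed is an analysis error.* Contrasts are commonly set out in a SAP or full protocol, neither of which is shown.
- *That selecting patients on low FVC or diffusing capacity biases the comparison through regression to the mean.* It acts on all randomised arms alike and cancels in expectation.

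**Conclusion.** The point holds as one of precision. Read as written, the primary analysis has change-score precision, and conditioning on the collected baseline value would cut the variance by 35% at r = 0.3, 25% at r = 0.5, 15% at r = 0.7 and 5% at r = 0.9. The direction is certain for every r < 1. The size rests on assumed correlations, equal variances at the two times and a continuous outcome. It is worth correcting because the better method costs nothing, but it does not threaten validity. The four-level group factor is not a fault.

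**What to change.** In Statistical Analysis, state that each continuous outcome at weeks 13 and 25 will be modelled on group (four levels), visit and group-by-visit, with the baseline value of that outcome and its interaction with visit as covariates. A practically equivalent choice is to include baseline as a response and constrain its mean to be equal across arms.

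Keep the four-level factor. For the combination hypothesis, estimate combination v exercise alone and combination v herbal medicine alone from this model. Marginal main effects, and the interaction with its confidence interval, may be reported as supportive. Note beside them that marginal effects equal the individual effects only without interaction, and that the interaction has about 64% power even at 0.8 SD.

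The cost is a wording change, to be made before unblinding, plus a degree of freedom or two per model. No new measurement or patient is needed, and the sample size can stand.
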